**Figure 4 figure4:**
[figure not shown]
Point of care recruitment and randomization.

**Figure 5 figure5:**
[figure not shown]
Shows initial mock-up of app.

### Study Population

Patients will be recruited at outpatient and inpatient facilities in an academic center through informational paper and electronic flyers. Once enrolled, patients will receive a walkthrough of the app, which includes access to a training video. The provider dashboard will also have access to the training video. Eligible patients will be 18 years or older, have a mobile phone or access to the Internet at home, and be able to complete a Web-based questionnaire in English. Exclusion criteria include the inability to communicate with the investigators and comply with the study requirements, presence of short bowel syndrome or stoma, and presence of a condition or disease that, in the opinion of the investigators, may make it difficult for the patient to use the HealthPROMISE app, including, but not limited to, advanced dementia.

### Study Instruments

#### Overview

A combination of different questionnaires (eg, SIBDQ), symptom updates, and quality indicators relevant for evaluating patient status will be the data collected during this study through the HealthPROMISE app (Figure 6).

**Figure 6 figure6:**
[figure not shown]
Shows completed app.

#### Disease Specific Quality of Life Questionnaire

The Short Inflammatory Bowel Disease Questionnaire (SIBDQ) [20] is a validated and reliable tool to measure health-related QOL in adult patients with IBD. The questionnaire consists of 10 questions scored in four domains: bowel symptoms, emotional health, systemic systems, and social function. The SIBDQ is a respected QOL questionnaire used extensively in academic research and clinical trials. Study patients in the control arm and interventional arm will complete an SIBDQ as part of a survey to objectively measure QOL at baseline and at exit (52 weeks or 104 weeks). Additionally, patients in the intervention arm will be asked to complete the SIBDQ every 2 weeks; this will be used to classify patients as having “good control,” “fair control,” or “poor control.”

#### General Quality of Life Questionnaire

EQ-5D is a standardized instrument for measuring generic QOL [21]. Applicable to a wide range of health conditions and treatments, it provides a simple descriptive profile and a single index value for health status. EQ-5D is primarily designed for self-completion by respondents. It is cognitively simple and takes only a few minutes to complete. It is generally recognized that a change of 0.5 points (on a scale of 1-7) is the minimal clinically important difference (MCID), consistent with moderate effect size. Patients in the intervention arm will be asked to complete the EQ-5D every 2 weeks.

#### Other Instruments

eHEALS is an 8-item measure of eHealth literacy developed to measure consumers’ combined knowledge, comfort, and perceived skills at finding, evaluating, and applying electronic health information to health problems [22]. This instrument has been psychometrically validated and its score positively correlated with intention to use personal health records. Patient Activation Measure (PAM-13) will be used to measure patient activation and engagement with health [23]. eHEALS and PAM-13 will be completed by patients in both arms during entry and exit surveys only.

Quality indicators are included from a list of indicators published by national societies and finalized through a Delphi panel of IBD providers [24,25]. These will be updated every three months by either providers or patients, along with hospitalization and emergency department visit information (Figure 7).

Utilization will be assessed through log-in, page views, health information updates, and response to alerts and reminders.

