**Methods:**

Participants will be recruited during face-to-face visits and randomized to either an interventional (ie, HealthPROMISE) or control (ie, education app). Patients in the HealthPROMISE arm will be able to update their information and receive disease summary, quality metrics, and a graph showing the trend of QOL (SIBDQ) scores and resource utilization over time. Providers will use the data for collaborative decision making and quality improvement interventions at the point of care. Patients in the control arm will enter data at baseline, during office visits, and at the end of the study but will not receive any decision support (trend of QOL, alert, or dashboard views).

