## Methods

### Study Design

This is a phase III, single-center, pragmatic randomized controlled trial (RCT) to evaluate if a patient-centric self-monitoring and collaborative decision support platform will lead to sustainable improvement in overall QOL for IBD patients. It is intended that 300 patients with IBD will be recruited into the study (allocation ratio 1:1; Figure 4). After meeting all the inclusion criteria with no exclusions, patient is asked to complete a tablet-based screening questionnaire at the end of which patient is randomized at the point of care to intervention or control arm. Patients in the control arm will receive an IBD education app PIN whereas the intervention arm will receive HealthPROMISE app PIN (Figure 3). Intervention patients enter their data once every 2 weeks and this data is then made visible to providers using a Web-based dashboard integrated with the EHR (Figures 4 and 5). Intervention and control apps will be provided free of charge to patients, and patients will be given $25 after completing initial and end of study questionnaires.

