## Results

### Outcome Measures

All outcome data (Textbox 1) will be collected online. Additionally, we will conduct subgroup analysis of patients with poor disease control at week 0 (SIBDQ≤30) and in those with high patient-reported anxiety, depression, or stress achieving primary and secondary endpoints. We will assess change in inflammatory markers, endoscopic scores, and additional quality metrics in each group and determine predictors of HealthPROMISE and control app utilization and its impact on other primary and secondary end-points. Consistent with the pragmatic nature of the trial, study progress will be assessed throughout and effort will be optimized to better engage providers and patients (Table 1).

Primary and secondary endpoints.Primary endpointNumber of quality indicators met in HealthPROMISE versus control armSecondary endpoints
_Decrease in number of emergency visits due to IBD_

_Decrease in number of hospitalization due to IBD_

_Change in generic QOL score (EQ-5D) from baseline_

_Proportion of patients in each group who meet all eligible outpatient quality metrics_

_Proportion of patients in disease control in each group_

_Emergency visits in each group_

_Hospitalizations in each group_

_General QOL scores in each group_

_Per protocol analysis of intervention patients with adequate HealthPROMISE use (more than 6 log-ins with data entry from week 0 through week 52) achieving above mentioned primary and secondary endpoints_

**Table 1 table1:** Evaluation metrics for HealthPROMISE progress

Metric		Target Group	Goal / Timeline

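### The article describes a different recording route, schedule and feedback by arm for the quality indicators, emergency visits and hospitalizations, so fuller recording under HealthPROMISE could appear as more indicators met

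*Protocol article*

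**What the plan says.** The primary endpoint is the number of quality indicators met, compared between arms. Emergency visits and hospitalizations are secondary endpoints (Outcome Measures). How these are recorded is spread over several places:

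- **Route.** Study Instruments, Overview lists questionnaires, symptom updates and quality indicators and says these "will be the data collected during this study through the HealthPROMISE app". Study Design states: "Patients in the control arm will receive an IBD education app PIN whereas the intervention arm will receive HealthPROMISE app PIN". Outcome Measures adds: "All outcome data (Textbox 1) will be collected online". The route for control-arm entry is not named.
- **Recorder and schedule.** Other Instruments says of the indicators: "These will be updated every three months by either providers or patients, along with hospitalization and emergency department visit information". No arm is named. The abstract's Methods paragraph says: "Patients in the control arm will enter data at baseline, during office visits, and at the end of the study".
- **Feedback.** The same paragraph says: "Patients in the HealthPROMISE arm will be able to update their information and receive disease summary, quality metrics". Controls get no trends, alerts or dashboard. In Study Design, intervention patients enter data every 2 weeks and "this data is then made visible to providers using a Web-based dashboard integrated with the EHR".
- **Scoring times.** Statistical Analysis Plan, Overview computes the percentage of eligible metrics met at baseline and at week 104, and takes the change.

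**The concern.** Taken together, these statements make the tool under test also the stated recorder of the primary endpoint. An indicator can become met because the care was given, or because someone updated a field showing that it was given. HealthPROMISE shows patients their metrics and shows providers the patient's data, so it may encourage both. If controls are recorded by another route and on another schedule, the between-arm difference mixes the effect on care with the effect on recording.

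The possible recorders are patients and providers. The article makes no statement on blinding, but patients know which app they have, and the dashboard shows providers who is in the intervention arm. That they can tell the arm is therefore an inference from the design, though a safe one.

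The direction depends on the endpoint. For indicators, fuller recording in the intervention arm favours HealthPROMISE. For emergency visits and hospitalizations it adds events to that arm and works against HealthPROMISE.

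**Working it through.** **1. Can the statements be read consistently?**

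- If the three-monthly update covers the intervention arm only, the schedule differs by arm.
- If it covers both arms and patients make it, it conflicts with the control schedule in the abstract, and the Overview names an app that controls do not have.
- If it covers both arms and providers make it for controls, the schedule agrees. But patients may still make the entries in the intervention arm, so the recorder may differ.
- Only if the same kind of recorder made the same update in both arms would ascertainment match. The article does not say so.

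**2. The plan's own figure.** Sample Size Justification assumes 85% v 70% meeting all indicators, 80% power and a one-sided 5% level. With pooled variance and no continuity correction:

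n = [1.645 × √(2 × 0.775 × 0.225) + 0.842 × √(0.85 × 0.15 + 0.70 × 0.30)]² / 0.15² ≈ 95 per arm

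This reproduces the stated 95. It says nothing about recording, but it fixes the yardstick: a 15-point effect.

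**3. How far could recording alone move the result?** The documents give neither recording accuracy nor the number of eligible indicators, so the inputs here are assumptions. Let true care be equal in both arms. A met indicator is recorded with probability s, misses are independent, and no unmet indicator is recorded as met.

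*Percentage score.* If a share m of eligible indicators is truly met, the false difference at week 104 is m × (s_int − s_ctl).

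- 99% v 97%: m × 2 points, so at most 2 (1.4 at m = 70%).
- 99% v 95%: m × 4 points, so at most 4 (2.8 at m = 70%).

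Subtracting baseline does not remove this if baseline is recorded alike in both arms.

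*All indicators met.* With k eligible indicators and 70% truly meeting all, the false difference is 0.70 × (s_int^k − s_ctl^k).

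| k | s_int v s_ctl | Recorded as meeting all | False difference |
|---|---|---|---|
| 5 | 99% v 97% | 66.6% v 60.1% | 6.5 points |
| 5 | 99% v 95% | 66.6% v 54.2% | 12.4 points |
| 8 | 99% v 97% | 64.6% v 54.9% | 9.7 points |
| 8 | 99% v 95% | 64.6% v 46.4% | 18.2 points |

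**4. Effect on the test.** With 95 per arm, a one-sided 5% level and equal true care, suppose a given share of control patients who truly meet all indicators is not recorded as doing so. The chance of a false benefit is then:

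| Shortfall in controls | True rate 85% | True rate 70% |
|---|---|---|
| none | 5% | 5% |
| 5% | 19% | 13% |
| 10% | 44% | 27% |

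No figure is offered for emergency visits or hospitalizations, because the documents give no event rates.

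**The case against.** The strongest reply is that a one-arm collection scheme is nowhere stated. Other Instruments names no arm for the three-monthly update, whereas the sections on SIBDQ and EQ-5D do name the intervention arm for their two-weekly schedules. Table 1 lists the readmission rate in two arms under quarterly reports, which suggests that hospitalizations are followed quarterly in both. Controls do enter data, outcome data are collected online, and the metric is scored at baseline and week 104, close to times when both arms enter data. A condensed article may also leave source rules to the full protocol.

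Most of this stands, and it limits the point. A reader might infer that controls have no outcome data, that intervention patients get up to eight prompted chances over 104 weeks to have an indicator marked as met, or that controls must recall events over a year or more. The documents support none of these. Control entry is described, including at office visits. No rule counts an indicator as met if it was marked so at any quarterly update. Prompting for these updates is not described.

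The reply does not dispose of the point. The article does state a route, a recorder and a schedule, and what it states differs between arms or conflicts between sections. That is more than omitted detail. A pragmatic design allows routine data sources, but gives no reason for ascertainment that differs by arm.

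**Conclusion.** The concern holds as a described difference between arms in route, schedule and feedback for endpoints that people aware of the arm may record. If the text is followed as written, fuller recording under HealthPROMISE can raise the number of indicators met without any change in care.

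The size is unknown. Under the assumed recording rates it is at most about 2 to 4 points on the percentage score, and 6.5 to 12.4 points on the all-met version with 5 indicators and 70% truly meeting all. The larger figures should not be read as estimates for the primary endpoint. They rest on assumed recording rates, an assumed number of indicators and independent misses. They also apply only to the all-met version, which Sample Size Justification calls primary but Outcome Measures lists as secondary.

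It would also be wrong to conclude that every endpoint is tilted towards HealthPROMISE, since for emergency visits and hospitalizations the direction is reversed.

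**What to change.** Reconcile the abstract's Methods paragraph, Study Instruments Overview and Other Instruments. Then state one rule: indicators, emergency visits and hospitalizations are scored for every randomised patient, including those who stop using their app, from the same source, form, time points and look-back window in both arms.

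Either of two routes would do:

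- The same three-monthly update in both arms, made by the same kind of recorder, without feedback to controls.
- The same EHR fields read at baseline and week 104. Because the dashboard is integrated with the EHR, these should be fields that app entries do not fill.

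App entries available in only one arm should serve to deliver the intervention, not to score the between-arm endpoint. Long-recall exit questionnaires are a poor substitute for counting events.

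The cost is protocol wording and one common extraction or update rule. The three-monthly route adds data entry for controls. Some intervention-arm detail goes unused in the comparison. An EHR source may miss events at other institutions, but the rule for finding them would be the same in both arms.

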**Figure 7 figure7:**
[figure not shown]
Provider workflow on app dashboard.

## Results

### Outcome Measures

All outcome data (Textbox 1) will be collected online. Additionally, we will conduct subgroup analysis of patients with poor disease control at week 0 (SIBDQ≤30) and in those with high patient-reported anxiety, depression, or stress achieving primary and secondary endpoints. We will assess change in inflammatory markers, endoscopic scores, and additional quality metrics in each group and determine predictors of HealthPROMISE and control app utilization and its impact on other primary and secondary end-points. Consistent with the pragmatic nature of the trial, study progress will be assessed throughout and effort will be optimized to better engage providers and patients (Table 1).

Primary and secondary endpoints.Primary endpointNumber of quality indicators met in HealthPROMISE versus control armSecondary endpoints
_Decrease in number of emergency visits due to IBD_

_Decrease in number of hospitalization due to IBD_

_Change in generic QOL score (EQ-5D) from baseline_

_Proportion of patients in each group who meet all eligible outpatient quality metrics_

_Proportion of patients in disease control in each group_

_Emergency visits in each group_

_Hospitalizations in each group_

_General QOL scores in each group_

_Per protocol analysis of intervention patients with adequate HealthPROMISE use (more than 6 log-ins with data entry from week 0 through week 52) achieving above mentioned primary and secondary endpoints_

**Table 1 table1:** Evaluation metrics for HealthPROMISE progress

Metric		Target Group	Goal / Timeline

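### The planned analysis of how app use affects the endpoints counts health information updates as use, while the quality indicators and events can be recorded through such updates, so a recording artefact could be read as an effect

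*Protocol article*

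**What the plan says.** Under Other Instruments, the protocol article defines the exposure: "Utilization will be assessed through log-in, page views, health information updates, and response to alerts and reminders". The paragraph just before it says of the quality indicators: "These will be updated every three months by either providers or patients, along with hospitalization and emergency department visit information". The Overview of Study Instruments lists questionnaires, symptom updates and quality indicators together and says that they "will be the data collected during this study through the HealthPROMISE app". Outcome Measures adds: "All outcome data (Textbox 1) will be collected online".

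Outcome Measures then plans, beyond the listed endpoints, to "determine predictors of HealthPROMISE and control app utilization and its impact on other primary and secondary end-points".

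The arms differ in how often data are entered. Study Design says "Intervention patients enter their data once every 2 weeks". The Abstract says "Patients in the control arm will enter data at baseline, during office visits, and at the end of the study", and that controls "will not receive any decision support (trend of QOL, alert, or dashboard views".

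The Statistical Analysis Plan section scores each patient as metrics met divided by metrics eligible, times 100, at baseline and week 104. It does not say how an eligible indicator with no entry is scored.

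**The concern.** The exposure includes a count of updates, and the outcomes reach the database through updates. If the patient makes those entries, someone who enters more is a heavier user by definition and also has more indicators and more events on record. An association then arises without any change in care. Calling it an impact gives it a causal reading that randomisation does not protect, because use is not randomised.

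For the quality indicators, the artefact could be taken as evidence that greater use of the app brings better care. For hospitalizations and emergency visits it runs the other way: more entry means more recorded events, so use could look harmful.

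A narrower problem concerns comparison across arms. Controls receive no alerts, so a measure that includes alert responses is not the same quantity in both arms.

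**Working it through.** **The plan's own figures.** The article gives no figure for this analysis. Its 95 per arm (85% vs 70%, one-sided 5%, 80% power) reproduces, but it concerns the randomised comparison and has no bearing here.

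**Where exposure and outcome can overlap.**
- Exposure: log-ins, page views, health information updates, responses to alerts and reminders (Other Instruments).
- Quality indicators and events: three-monthly updates by providers or patients (Other Instruments), collected online (Outcome Measures).
- Score: met / eligible × 100. Read literally, an eligible indicator with no entry stays in the denominator and adds nothing to the numerator.
- Nothing in the article separates outcome-bearing entries from the other updates.

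**Size under no effect of use.** From the documents: 150 per arm and 30% attrition, so 150 × 0.70 = 105 intervention patients. Assumed, because the article gives no values: 8 indicators per patient; 80% truly met, independently of use; updates per patient Binomial(8, p) with p from Beta(1.5, 1.5); a fraction f of met indicators on record only through an update; a 40% chance per update of recording such an indicator.

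Expected recorded score after u updates = 80 × (1 − f × 0.6^u).

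The mean of 0.6^u is 0.484 among patients with 3 or fewer updates and 0.046 among those with 5 or more. The expected gap between high and low users is therefore 80 × f × (0.484 − 0.046) = 80 × f × 0.438. The last column comes from 3,000 simulated trials per scenario, with linear regression of the recorded score on updates, tested two-sided at 5%.

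| f | Gap, high minus low users (points) | Trials with use significant |
|---|---|---|
| 0% | 0 | 5% |
| 10% | 3.5 | about 27% |
| 20% | 7.0 | about 72% |
| 30% | 10.5 | about 95% |

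**Dependence on the recording rule.** A second null simulation used rank correlations, with 105 patients, 8 indicators each 85% truly met, 0.6 hospitalizations per patient, entry propensity Beta(2, 1.5) and 2,000 runs. All of these inputs except the 105 are assumed.

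| Recording | Use vs quality score | Use vs hospitalizations |
|---|---|---|
| Patient entry only; no entry = unmet | +0.76 (about 100% significant) | +0.20 (57%) |
| Providers also record half | +0.53 (about 100%) | +0.08 (13%) |
| Unrecorded indicators leave the denominator | −0.12 (25%) | +0.21 (57%) |
| Outcomes recorded independently of use; outcome entries not counted as use | 0.00 (5%) | 0.00 (5%) |

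The negative value in the third row arises because a patient with few recorded indicators reaches 100% more easily: 85% of the time with one indicator, 0.85^8 = 27% with eight.

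**Do log-ins alone solve it?** With the first set of assumptions and f = 10%, 20%, 30%, the exposure was replaced in two ways. Taking log-ins as updates plus Poisson(6) view-only visits gave false significance in about 15%, 40% and 70% of trials. Taking early log-ins (6 opportunities, same individual propensity) gave 15%, 43% and 72%. The bias shrinks but remains, because the patients who log in are those who enter data.

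**The case against.** The strongest reply is that the overlap is inferred. The article never itemises health information updates, and it lets providers record the indicators and events. If providers record everything regardless of patient use, the mechanism disappears. That stands as a condition. Against it, the article expects most data to come from patients (Future Direction and Sustainability), and with providers also recording half of the indicators the spurious correlation was still +0.53.

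A reader might infer more than the text supports:

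- **That use will appear to improve care.** This needs unrecorded indicators to count as unmet. That is the literal reading of met over eligible, but it is not stated. Without it there was no upward bias, and for events the direction is adverse. More EQ-5D or SIBDQ entries do not by themselves raise a score.
- **That alert responses share entries with the outcomes.** Nothing says that an alert response records an outcome, and Table 1 assigns response to alerts to providers. Only the lack of comparability across arms stands, and the Abstract's exclusion for controls names alerts, not reminders.
- **That a particular dose-response regression is planned.** The article names no model, coding or pooling across arms, and leaving those details to a fuller document is no fault.
- **That the simulated rates forecast this trial.** The dependent fraction and capture rate come from nowhere in the article. The first simulation also uses a cumulative score rather than the planned change from baseline to week 104. Only direction and rough size should be read from them.

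Finally, this is an additional analysis outside the listed endpoints, and the endpoints are assessed primarily by intention to treat. That limits its importance but does not make the stated exposure sound.

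**Conclusion.** The point holds in conditional form. As written, the utilization measure can contain the entries that supply the quality indicators, hospitalizations and emergency visits, and the analysis is described as one of impact. To the extent that patients make those entries, use can be spuriously associated with more indicators met (given that unrecorded counts as unmet) and with more recorded events. Under the assumed inputs, the false-positive rate for the quality score runs from 5% with no dependence on updates to about 95% when 30% of met indicators depend on them, with gaps of 0 to about 10.5 points between high and low users.

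The randomised intention-to-treat comparison and the sample size are untouched. The change is worth making because it is cheap and because a result labelled an impact would invite a causal reading.

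**What to change.** For this analysis only:

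1. Leave outcome-bearing entries (quality indicators, hospitalizations, emergency visits and questionnaire scores used as endpoints) out of the utilization measure.
2. Leave alert responses out of any comparison of use across arms.
3. Use only outcome values recorded on the schedule common to both arms (baseline and exit) or by providers, so that recording does not depend on the patient's use.
4. Adjust for baseline SIBDQ, disease severity, eHEALS and PAM-13, which the article already plans to collect or model.
5. Report the result as an association, not an impact.

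Restricting the measure to log-ins and page views is not enough without step 3. Using randomised arm as an instrument for use is not a safe alternative unless outcomes are recorded in the same way in both arms: the entry schedules differ, so arm could affect recording directly.

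The cost is a change of wording and a little analysis work. The downside is a narrower utilization measure and a less precise estimate. Engaged patients may still differ in ways that the baseline measures miss, which is why the result should be called an association.

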### Statistical Analysis Plan

#### Overview

We will use SAS 9.2 (SAS Institute, Inc) to calculate frequencies and percentages for categorical factors and means with standard deviations and/or percentiles for continuous factors. Pearson’s chi-square tests will be used for primary outcome (number of quality indicators met in HealthPROMISE vs control arm) and secondary outcomes. We will calculate percentage score for each patient at baseline and at week 104 ([number of quality metrics met/quality metrics eligible]*100). Change in the percentage score from baseline to week 104 will be aggregated for each arm to calculate percentage-point improvement in quality metric, similar to the strategy by Cebul et al [26].

Analysis of covariance (ANCOVA) will be performed to assess differences in the area under the curve of QOL scores while adjusting for baseline QOL score. To assess the association between patient and practice characteristics and achievement of eligible quality metrics, we will use multivariable analyses. Since the data will be hierarchically structured, with patients clustered within physicians and metrics clustered within patients, we will construct multilevel, generalized, linear mixed models with random effects to determine predictors of quality care, similar to the strategy used by Kanwal et al [27]. Independent variables will include demographic characteristics (age, gender), education and income level, race and ethnicity, computer usage, eHealth literacy scores, clinical characteristics (comorbidities, phenotype, disease severity), and provider characteristics (gender, age, site of practice, years of practice, presence of nurse practitioner).

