#### Interim Analysis

Interim analysis will be performed once 150 patients are followed up for week 52. If primary outcome is met by that time, all patients will be offered HealthPROMISE app and followed for the additional 52 weeks.

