#### Sample Size Justification

Study endpoints will be primarily assessed using intention-to-treat (ITT) analysis; however, per-protocol analysis will also be performed. The study is to be powered such that there is a>80% probability of demonstrating a difference with a *P* value *(P* = .05) using a two-tailed *t* test.

We assume that 128 out of 150 subjects (85%) in the intervention arm will meet all quality indicators (primary outcome) and expect that this percentage will be at least 15% lower in the control arm. A sample size of 95 patients will be needed in each arm to achieve at least 80% power to detect the difference with a 5% one-sided significance level.

Accounting for an estimated 30% attrition rate, we will require a total of 250 IBD patients to be enrolled in the study. Since some patients may agree to enroll but not download the app or use the PIN, we will recruit a total of 300 patients in the study.

For secondary outcomes related to QOL, the control arm is not a placebo arm and physicians are free to initiate any therapy based on patients' symptoms. Hence, we will assess the difference in proportion of patients achieving MCID in the HealthPROMISE arm versus control arm in the study. Using the distribution-based approach, an effect size of 0.5 SD is the closest estimate for determining MCID for SIBDQ and EQ-5D. Assuming that 20% more patients in HealthPROMISE arm will achieve MCID than in the control arm, the sample size of 250 patients will have 88% power to detect the difference with a 5% one-sided significance level and an estimated 30% attrition rate.

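### Emergency visits and hospitalizations are compared without regard to time observed, although 30% attrition is expected; unequal loss between arms would appear as a difference in events

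*Protocol article*

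**What the plan says.** In the Protocol article, Outcome Measures (Textbox 1), the resource-use endpoints are "Decrease in number of emergency visits due to IBD" and "Decrease in number of hospitalization due to IBD". The same two outcomes appear again lower in the list in a by-group form, for example "Hospitalizations in each group". No entry gives a rate, a person-time denominator or a counting window.

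Under Statistical Analysis Plan, Overview, Pearson "chi-square tests will be used for primary outcome (number of quality indicators met in HealthPROMISE vs control arm) and secondary outcomes". The mixed models described there are for predictors of quality care, not for these events.

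Sample Size Justification makes intention to treat the main analysis and sets the enrolment target after "Accounting for an estimated 30% attrition rate". It does not split that figure by arm.

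Contact differs by arm. Intervention patients enter data every 2 weeks (Study Design). Control patients do so at baseline, at office visits and at the end of the study (Abstract, Methods). Other Instruments says that hospitalization and emergency department information is updated every three months by providers or patients.

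**The concern.** A count of events depends on how long the patient was observed. A plan that expects three patients in ten to leave, keeps them in an intention-to-treat comparison and names a test with no exposure term treats short and long observation alike. The arm with less observation time then records fewer events even when the true rates are equal.

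Unequal observation is plausible here because the two arms have different reporting burdens and different reasons to stay engaged. Fortnightly entry might drive intervention patients away. An education app without decision support might fail to hold control patients, or sparser contact might miss some of their events. These mechanisms push in opposite directions.

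Resource utilization is named in the objective and in the hypothesis restated in the Discussion, so a spurious difference in admissions would bear on one of the trial's stated claims.

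**Working it through.** **Figures in the plan.** The article gives no event rate, sample size or power for these two outcomes, so there is no figure of its own to reproduce. Its 95 per arm concerns the quality-indicator endpoint.

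**Inputs from the article.** 300 patients allocated 1:1, hence N = 150 per arm (Study Design); a 2-year study period, hence T = 2 years (Principal Findings); 30% attrition overall (Sample Size Justification).

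**Assumptions, not in the article.** Equal true event rates in both arms; patients who leave do so uniformly over follow-up, so on average at mid-study; arm-specific losses a_I and a_C that average 30%.

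**Formula.** Person-years per arm = N × T × (1 − a/2). With equal rates, the expected ratio of raw counts is the ratio of person-years:

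R = (1 − a_I/2) / (1 − a_C/2)

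For example, at 40%/20%: 300 × 0.80 = 240 and 300 × 0.90 = 270 person-years, so R = 240/270 = 0.89.

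The last column is a more extreme case in which patients who leave contribute no data: R = (1 − a_I)/(1 − a_C).

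| Loss, intervention / control | Person-years | R, mid-study loss | R, leavers contribute nothing |
|---|---|---|---|
| 30% / 30% | 255 / 255 | 1.00 | 1.00 |
| 35% / 25% | 247.5 / 262.5 | 0.94 | 0.87 |
| 40% / 20% | 240 / 270 | 0.89 | 0.75 |
| 25% / 35% | 262.5 / 247.5 | 1.06 | 1.15 |
| 20% / 40% | 270 / 240 | 1.13 | 1.33 |

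**Effect on error rates.** In 10,000 simulated trials per scenario, events were overdispersed (gamma-Poisson), true rates were equal at an assumed 0.2 or 0.4 per year, and drop-out was unrelated to event risk. The table shows how often the intervention was falsely favoured at 5% one-sided; the two values in each cell are for the rates 0.2 and 0.4.

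| Loss, intervention / control | Raw counts per randomized patient | Events per person-year |
|---|---|---|
| 30% / 30% | 5.1%, 5.2% | 5.1%, 5.2% |
| 35% / 25% | 8.2%, 9.4% | 5.2%, 5.3% |
| 40% / 20% | 13.1%, 14.8% | 5.4%, 4.9% |

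The raw-count test here compares mean counts. A chi-square on patients with or without an event would give different figures.

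**The case against.** The strongest case against is that the textbox entries are labels. A condensed article may leave counting windows and offsets to a full protocol or a separate analysis plan, and nowhere does it say that missing reports count as zero events. That would dispose of the point if it rested on silence. But the article itself names a test for secondary outcomes, and that test has no exposure term. The stated analysis therefore needs correcting. Table 1 does mention a readmission rate by arm, but as a progress metric, not as one of these endpoints.

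Several parts of the objection stand, and they rule out stronger readings:

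- **A bias in a known direction.** A reader might infer that the intervention will look falsely better. The article gives no loss by arm; equal loss gives no between-arm bias, and the reverse imbalance favours control.
- **Exit at 52 or 104 weeks as a further cause of bias.** The wording "at baseline and at exit (52 weeks or 104 weeks" concerns the SIBDQ survey. It may follow for the whole trial from the interim rule: "If primary outcome is met by that time, all patients will be offered HealthPROMISE app and followed for the additional 52 weeks". If so, randomization balances it. It would bias the comparison only if its mix differed by arm.
- **Withdrawn patients cannot be told from event-free ones.** The three-monthly updates would show a gap, and providers can enter events. The information may well exist; the named test does not use it.
- **An overstated within-patient decrease even with equal loss.** This needs a baseline count and zero-filling after withdrawal, and the article states neither.
- **Four affected endpoints.** There are two outcomes, each listed twice.

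If the chi-square is applied to patients with any event, the count ratio is also not the quantity tested. Shorter observation still lowers the proportion with an event.

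**Conclusion.** The point holds as a weakness in the stated analysis of two secondary outcomes: their definition and the test named for them ignore time observed, in a trial that expects 30% attrition. It is not a demonstrated bias. Under equal true rates and mid-study loss, a 10-point attrition gap shifts the count ratio by about 6% and a 20-point gap by about 11 to 13%, towards whichever arm is observed less. The shift is nil if loss is equal, and larger if leavers contribute no data. Arm-specific losses, timing of drop-out and event rates are all assumed. The primary endpoint is untouched. The change should be made because it is cheap and gives a better comparison, and it should be fixed before outcome data are analysed.

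**What to change.** - Define both outcomes once each, as events per patient-year from randomization to the last confirmed follow-up, over one stated window that also says how time after a positive interim result is handled.
- Analyse them with a count model with log follow-up time as offset, for example negative binomial, or Poisson with robust errors, in place of the chi-square test.
- Use the three-monthly updates to date the end of observation for each patient.
- If a decrease is to be reported, compute it as this rate against the rate in a pre-randomization period of fixed, stated length.
- Report follow-up time and attrition by arm.

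The cost is one date field per patient and slightly more analysis work, with no extra visits. One limit remains: the offset corrects for unequal time observed but not for drop-out that is itself related to event risk.
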